## Abstract

**Background::**

Cervical Spondylotic radiculopathy (CSR) is the most common spinal degenerative disease. Its clinical manifestations are pain and numbness in the neck and arm and limitation of neck movement, which greatly affects the life and work of patients. Acupuncture and electroacupuncture are commonly used in China, the efficacy of acupuncture has been confirmed. Existing evidence shows that electroacupuncture seems to be better than acupuncture, but there is a lack of clinical research to directly compare the two.

**Methods::**

This is a prospective randomized controlled trial to compare the efficacy of electroacupuncture and acupuncture in the treatment of CSR and to explore the safety and potential mechanism of electroacupuncture in the treatment of CSR. Approved by the Clinical Research Ethics Committee of our hospital, the patients are randomly divided into an experimental group (electroacupuncture group) or control group (acupuncture group). The patients are followed up for 30 days after 4 weeks of treatment. Observation indexes included VAS score, Neck Disability Index, Yasuhisa Tanaka 20 Score Scale, adverse reactions and so on. Finally, the data will be analyzed by SPSS 18.0 software.

**Discussion::**

This study will directly compare the advantages and disadvantages of electroacupuncture and acupuncture in the treatment of CSR. The results of this study will help to guide patients with CSR to choose appropriate treatment.

**Trial registration::**

OSF Registration number: DOI 10.17605/OSF.IO/9MKPN

## Introdoction

1

Cervical spondylosis is a very common disease. Cervical Spondylotic radiculopathy (CSR) is one of the most common types, accounting for about 60% to 70% of all cervical spondylosis.^[1]^ Every year, about 1.6 million people around the world suffer from dysfunction, which seriously affects the quality of life.^[2]^ CSR is mainly due to degenerative changes such as protrusion or prolapse of nucleus pulposus, hyperosteogeny of posterior facet joint or bone spur formation of uncinate joint, which cause stimulation and compression to spinal nerve root and appear corresponding symptoms and signs.^[1,3]^ Due to the aging of the population, the change of life style and the increase of work or life pressure, the incidence of CSR is increasing year by year.^[4]^ Its clinical manifestations are mainly neck, arm pain, numbness, limited neck movement, seriously affecting people's life and work.^[5]^

The main purpose of CSR treatment is to relieve pain, numbness and discomfort, improve function and improve quality of life. At present, conservative treatment is still the main treatment of CSR, but the traditional treatment is limited because of its low efficacy.^[6]^ These treatments include non-steroidal anti-inflammatory drugs (NSAIDs),^[7]^ muscle relaxants,^[8]^ epidural steroid injections,^[9]^ physical therapy^[10]^ and so on. With the exploration of complementary and alternative therapies, traditional Chinese medicine intervention methods, such as Chinese herbal medicine,^[11]^ cupping therapy,^[12]^ acupuncture,^[13]^ massage,^[14]^ have been widely used in the treatment of cervical spondylosis, among which acupuncture is the most popular treatment. There has been evidence that acupuncture has significant anti-inflammatory and analgesic effects, and can significantly improve the quality of life of patients with CSR.^[15]^

Electroacupuncture is a therapy which adds electrical stimulation on the basis of acupuncture. It has been widely used in bone and joint diseases, and has been proved to be effective in some cases of failure of traditional acupuncture treatment.^[16]^ It combines the meridian theory of traditional acupuncture and the advantages of low-frequency current, and can set the frequency and intensity of stimulation. Clinical studies have shown that electroacupuncture increases the expression of integrin β 1 and Aktinhibits by inhibiting TNF--TNFR1-caspase-8 signal pathway, and inhibits the apoptosis of AF cells, which have been proved to be a good alternative therapy for cervical spondylosis.^[17]^ Based on the current evidence, it is speculated that the effect of electroacupuncture on CSR may be better than that of traditional acupuncture. However, there is still a lack of clinical research on the direct comparison of the two treatments in the treatment of CSR. Therefore, we intend to use this randomized controlled trial to evaluate the advantages and disadvantages of the two treatments in the treatment of CSR, and to explore the safety and potential mechanism of electroacupuncture in the treatment of CSR.

## Materials and methods

2

### Study design

2.1

This is a prospective randomized controlled trial to compare the efficacy of electroacupuncture and traditional acupuncture in the treatment of CSR, and to study the efficacy and safety of electroacupuncture in the treatment of CSR. This experiment will follow the Standards for Reporting Interventions in Clinical Trials of Acupuncture^[18]^ and the comprehensive trial report standard.^[19]^ The flow chart is shown in Figure 1.

**Figure 1 F1:**
[figure not shown]
Flow diagram.

### Ethics and registration

2.2

This research scheme is in line with the Helsinki Declaration and has been reviewed by the Clinical Research Ethics Committee of our hospital. This lab has been already registered in OSF (registration number: DOI 10.17605/OSF.IO/9MKPN). Before being randomly divided into groups, all patients are required to sign an informed consent form, and they can choose whether or not to continue the trial at any time.

### Sample size

2.3

The calculation of sample size is based on the mean and standard deviation of the visual analogue scale (VAS)^[20]^ score after treatment. According to the results of the pre-experiment, the experiment group is 2.41 ± 1.49, and the control group is 3.25 ± 1.28. Set α = 0.025, unilateral test, β = 0.10. Calculated by PASS15.0 software, each group needs 59 participants, with an estimated withdrawal rate of 10%, and each group will include 66 participants.

### Patients

2.4

Inclusion criteria: ① conforms to the diagnosis of cervical spondylotic radiculopathy (diagnosis refers to the diagnosis criteria of cervical spondylopathy issued by Chinese Rehabilitation Medical Association (2010) ^[21]^); symptoms and signs of ② include pain and numbness along the spinal nerve roots with positive foraminal compression and/or brachial plexus pull tests. Imaging (cervical spine X-ray, magnetic resonance imaging or computed tomography) consistent with clinical symptoms; ③ age 18–70 years; ④ not receiving acupuncture or other physical or medical treatment within 7 days; ⑤ signing informed consent form.

Exclusion criteria: ①other types of cervical spondylosis, such as vertebral artery type cervical spondylosis, sympathetic cervical spondylosis, cervical Spondylotic myelopathy, etc.; ②patients with history of neck trauma, neck fracture or operation; ③serious systemic complications such as cardio-cerebrovascular disease, tumor, diabetes, kidney disease or digestive system disease; ④pregnancy or lactation; ⑤refusal or fear of acupuncture.

### Randomization and Blinding

2.5

Random sequences will be generated by SAS 9.3 software (SAS Institute, Cary, NC, USA) by independent statisticians who do not participate in the implementation of the experiment or statistical analysis. Eligible participants will be randomly assigned to the electroacupuncture group or acupuncture group according to a 1:1 ratio. The clinical research coordinator entered participant information on the tablet and is given a random number. The research assistant gets the allocation of participants from the computer. Throughout the study, the research assistant is responsible for screening, recruiting participants, and assigning random numbers to participants who have been included. The outcome evaluator is responsible for the evaluation of the scale. Considering the actual operational nature of acupuncture, participants and practitioners may be aware of random distribution. However, the evaluators of research results and the statisticians of data statistics and analysis do not know about the distribution.

### Intervention measures

2.6

Control group: patients take proper posture and fully expose the operation site, and the acupuncture site is locally sterilized with 75% alcohol. The acupuncture points are: Dazhui (GV 14,1 point), Fengchi (GB 20, bilateral), Cervical Jiaji Points (EX-B2, bilateral), Jianjing point (GB 21, bilateral),) using disposable stainless steel acupuncture needle (Suzhou Hualun Medical Appliance Co., Ltd, Suzhou, China). Acupuncture is performed by an acupuncturist with a license of traditional Chinese medicine and at least 3 years of clinical experience. Acupuncture manipulations are stimulated for 10 s to achieve the sense of “getting Qi”. The needles are retained for 30 min, 4 times a week for 4 weeks.

Experiment group: connected with SDZ-II electroacupuncture instrument (Suzhou Medical Appliance Factory, China; registration No. 20132270611) on the basis of the control group, using continuous wave, the frequency was 130∼260 times / min, current intensity is adjusted to the acceptable range of patients, generally at 1∼1.6 mA. Lasted for 30 min, 4 times a week for 4 weeks.

All patients are followed up for 30 days after treatment, and the curative effect is evaluated again through outpatient follow-up on the 15th day and the 30th day, and the score data are collected.

### Evaluation criteria and efficacy judgment

2.7

(1)Primary outcome measures: Pain is the most important clinical manifestations of CSR patients, the VAS^[20]^ will be used to evaluate patients’ pain changes, and VAS is often used to measure pain intensity.^[22]^ Patients will be asked to mark a point between 0 and 100, where 100 represent the greatest pain (rightmost) and 0 indicates no pain (leftmost).(2)Secondary Outcomes:①Neck Disability Index (NDI),^[23]^ which is one of the most commonly used indexes to evaluate the neck dysfunction of patients. The NDI score included 4 subjective symptoms (neck pain intensity, headache, attention, sleep) and 6 items related to activities of daily life (weightlifting, work, driving or cycling, entertainment, personal care, reading); ②Yasuhisa Tanaka 20 Score Scale,^[24]^ which is more specific to CSR, includes scores of sensation, muscle strength and other neurological functions in addition to pain.(3)Adverse Reactions: Nausea, dizziness, rash, allergy and other discomforts occurred during the treatment.

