### Data collection and management

2.8

Two assistants collect and record the whole process of data during the study. Personal information about potential participants and registered participants will be collected, shared and stored in a separate storeroom to protect pre-trial, during and post-trial confidentiality. Access to the database will be limited to the researchers of this research team.

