### Statistical Analysis

2.9

The collected data are analyzed by SPSS 18.0 software. Chi-square test will be used for counting data, mean ± standard deviation () is used for measurement data, independent sample t test is used for normal distribution, Mann – Whitney *U* test is used for skewed distribution, and the difference was considered to be statistically significant when *P* *<* .05.

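### The adverse-reaction window closes with treatment, so new reactions in the 30-day follow-up are not counted although safety is an aim and two visits already take place

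*Protocol article*

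**What the plan says.** The protocol article makes safety an aim in three places. The Abstract (Methods) and the Introduction give one purpose as "to explore the safety and potential mechanism of electroacupuncture in the treatment of CSR", and section 2.1 (Study design) says the trial is "to study the efficacy and safety of electroacupuncture in the treatment of CSR".

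Section 2.7 (Evaluation criteria and efficacy judgment) gives the only definition of the safety outcome: "Nausea, dizziness, rash, allergy and other discomforts occurred during the treatment".

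Section 2.6 (Intervention measures) sets the time frame. Needling follows the schedule "The needles are retained for 30 min, 4 times a week for 4 weeks", and the electroacupuncture arm has the same number of weeks and sessions. Then: "All patients are followed up for 30 days after treatment". On what happens in that period, the same sentence continues: "the curative effect is evaluated again through outpatient follow-up on the 15th day and the 30th day, and the score data are collected".

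Section 2.8 (Data collection and management) adds a general statement: "Two assistants collect and record the whole process of data during the study". Section 2.9 (Statistical Analysis) names no safety comparison; it says only "Chi-square test will be used for counting data".

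**The concern.** Efficacy is assessed again at two visits after treatment, while harm, as worded, is counted only up to the end of treatment. No reason is given for judging benefit and harm over different periods.

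This is not a gap that the article leaves to a fuller document. The article states a time limit, and the limit does not fit the aim. Staff who follow it literally would have no reason to record a new reaction reported at the day-15 or day-30 visit. They would also have no instruction to note whether a reaction that began during treatment had resolved. The safety results would then describe the on-treatment period only, while the efficacy results run to day 30. A reader could easily take the safety results to cover the whole trial.

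**Working it through.** The documents give no adverse-reaction rate, expected count or safety sample size, so there is no planned safety figure to reproduce. The sample size in section 2.3 rests on the VAS score and has no bearing here. The check is a comparison of passages plus one small calculation.

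**1. Does the document separate treatment from follow-up?** Yes. Section 2.6 describes 4 weeks of sessions and places the 30 days after them. The time limit in section 2.7 therefore most naturally refers to the 4 weeks.

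**2. Does any other passage extend the safety window?** No.
- Section 2.6 describes the day-15 and day-30 visits by curative effect and score data, and does not mention adverse reactions.
- Section 2.8 refers to data over the whole study but does not name adverse events.
- The Abstract mentions the 30-day follow-up and then lists adverse reactions among the observation indexes, without saying when they are recorded.

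**3. How much observed time lies outside the window?** Inputs: 4 weeks of treatment and 30 days of follow-up (section 2.6).
- Treatment: 4 × 7 = 28 days
- Total observation: 28 + 30 = 58 days
- Inside the definition: 28/58 = 48%
- Outside the definition: 30/58 = 52%, including both follow-up visits

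**4. How much exposure lies outside the window?** None. All 4 × 4 = 16 sessions fall within the 28 days.

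**5. Which events are affected?**

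| Event | Under the wording of section 2.7 |
|---|---|
| Starts and ends during treatment | Counted |
| Starts during treatment and persists | Counted; later course not stated to be followed |
| New onset after the last session | Not counted |
| Worsening pain or neurological signs after treatment | Not labelled an adverse reaction, but visible in the day-15 and day-30 scores |

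**6. Can the number of missed reactions be estimated?** No. That needs an event rate and a distribution of onset times, and the documents give neither.

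**The case against.** The strongest reply is that an on-treatment window is a defensible choice for an exploratory safety aim. All 16 sessions fall inside it, and many reactions to needling may be immediate. The description of the follow-up visits sits in the intervention section and is not offered as a complete visit schedule. The general statement in section 2.8 and the list in the Abstract could be read as covering follow-up. This has some force: the text does not prove that staff would refuse to record a late event. It does not remove the point, because a general sentence on data collection does not override a specific definition. If the wider window is meant, section 2.7 should say so.

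Several stronger readings are tempting, and the documents do not support them.

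- **Persisting harm is excluded.** It is not. A reaction that began during treatment occurred during treatment and is counted. What is missing is any statement that its outcome is followed.
- **A flare after treatment is lost.** Pain is measured by the VAS, and the Tanaka scale covers sensation and muscle strength, so worsening should show in the scores at the follow-up visits.
- **Local needle or current effects are left out.** The named reactions are examples, and the definition ends with an open category that admits site pain, bruising or fainting. Whether such events are prompted is form-level detail that an article may leave to the full protocol.
- **Half of all harm is missed.** The 52% is a share of days and says nothing about how risk is distributed over them.
- **The trial will wrongly claim equal safety.** No passage plans such a conclusion, and section 2.9 names no safety comparison.
- **The sample is too small for safety, and the window makes this worse.** With zero events, the one-sided 95% upper bound on the true rate in one arm is 1 − 0.05^(1/66) = 4.4% for the 66 enrolled, or 1 − 0.05^(1/59) = 5.0% for the 59 expected to remain. These bounds depend on the number of patients and not on the length of the window, so they do not measure this defect.

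**Conclusion.** The point holds in a limited form. As worded, section 2.7 leaves out adverse reactions with onset after the last session, and the article does not say that reactions which began earlier are followed to their outcome. The uncounted period is 30 of about 58 observed days (52%) and includes both follow-up visits; the effect on the number of reactions cannot be computed.

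The conclusion assumes that the time limit in section 2.7 means the 4-week treatment period, as section 2.6 uses the term, and that staff follow it literally. If the authors meant the whole trial, the recording may be sound and only the wording needs correction. This is not an error in the analysis and does not affect the primary outcome. It is an inexpensive improvement to how well the trial can meet its own safety aim.

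**What to change.** Reword the definition in section 2.7 so that adverse events are counted from the first session to the day-30 visit. State in section 2.6 that the day-15 and day-30 visits record, in both arms alike, any new adverse event and the status of any that was unresolved. Report on-treatment and post-treatment events separately, so that the on-treatment result remains available and late events are visible without being mixed into it.

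The cost is a reworded definition and one more item on existing visit forms, with no added visits. The change should be made before follow-up visits begin, because late events that were not asked about cannot be recovered reliably afterwards.

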### Data collection and management

2.8

Two assistants collect and record the whole process of data during the study. Personal information about potential participants and registered participants will be collected, shared and stored in a separate storeroom to protect pre-trial, during and post-trial confidentiality. Access to the database will be limited to the researchers of this research team.

### Statistical Analysis

2.9

The collected data are analyzed by SPSS 18.0 software. Chi-square test will be used for counting data, mean ± standard deviation () is used for measurement data, independent sample t test is used for normal distribution, Mann – Whitney *U* test is used for skewed distribution, and the difference was considered to be statistically significant when *P* *<* .05.

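### Section 2.9 lets the observed distribution choose the test for primary VAS, so the hypothesis and effect measure are not fixed; at the documented SDs the numerical effect is small

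*Protocol article*

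**What the plan says.** Section 2.9 (Statistical Analysis) gives one rule for every continuous measure: an "independent sample t test is used for normal distribution", and the Mann-Whitney U "test is used for skewed distribution". It names no separate analysis for VAS, which section 2.7 makes the primary outcome, so the general rule governs the primary comparison. It does not say how normality is judged, or whether the check applies to each arm, each visit, the score or its change.

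Section 2.3 (Sample size) is tied to one branch only. It opens: "The calculation of sample size is based on the mean and standard deviation of the visual analogue scale". The pilot inputs are that "the experiment group is 2.41 ± 1.49, and the control group is 3.25 ± 1.28", with "Set α = 0.025, unilateral test, β = 0.10". The result is that "each group needs 59 participants", and, "with an estimated withdrawal rate of 10%, and each group will include 66 participants".

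Section 2.5 (Randomization and Blinding) states that those who analyse the data do not know the allocation.

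**The concern.** The two branches answer different questions. The t test addresses the difference in mean VAS. Mann-Whitney addresses whether scores in one arm tend to exceed those in the other, and it gives no mean difference on the scale used in section 2.3. If the arms differ in spread or shape, the rank test can reject when the means are equal. Under the rule as written, nobody can say before the data are collected which effect the primary P value will refer to. With no criterion for skewness, two analysts who follow the same text could also reach different branches.

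The switch is a practical possibility. VAS has a floor at 0, and the pilot mean in the electroacupuncture group is not far above it in SD units.

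**Working it through.** **1. Reproduce the planned size (inputs from section 2.3).**
- Difference: 3.25 − 2.41 = 0.84.
- Pooled SD: √[(1.49² + 1.28²)/2] = √1.929 = 1.389, so d = 0.84/1.389 = 0.605.
- Normal approximation, one-sided 0.025, power 0.90: n = 2(1.960 + 1.282)²/0.605² ≈ 57.5, so 58 per group.
- Exact two-sample t test (noncentral t): power 0.898 at 58 and 0.903 at 59, so 59 per group.
- Withdrawal: 59/0.9 = 65.6, so 66.

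The stated 59 and 66 are the t-test figures.

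**2. Size if Mann-Whitney were the test.** Its asymptotic relative efficiency under normality is 3/π = 0.955. 59/0.955 = 61.8, so 62 evaluable; 62/0.9 = 68.9, so 69 enrolled. At 59 per group its power is about 89%. The gap is 3 evaluable participants per group.

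**3. Distance from the floor.** Electroacupuncture: 2.41/1.49 = 1.62 SD above 0, so a normal model puts 5.3% of scores below 0. Acupuncture: 3.25/1.28 = 2.54 SD, about 0.6% below 0. Skew is plausible, but these figures do not establish it.

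**4. Simulation of the two-stage rule.** 59 per group, 6,000 trials per row, two-sided 5% tests. Assumptions that the protocol does not supply: the distribution shape; Shapiro-Wilk at 0.05 in either arm as the switch to Mann-Whitney; a 0 to 10 scale, as the pilot values suggest; and a common mean of 2.41 for the null rows.

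Pilot means and SDs (power):

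| Shape | t test | Mann-Whitney | Two-stage | Switch to rank test | Tests disagree |
|---|---|---|---|---|---|
| Normal | 90.6% | 89.1% | 90.3% | 10% | 3.4% |
| Normal clipped at 0 and 10 | 89.9% | 88.8% | 89.6% | 22% | 3.3% |
| Scaled beta on 0–10 | 89.5% | 93.1% | 93.0% | 85% | 4.4% |
| Gamma | 90.0% | 96.3% | 96.2% | 97% | 6.5% |

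Equal means (rejection rate):

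| Shape | Two-stage, SDs 1.49 and 1.28 | Two-stage, SDs 1.9 and 1.2 (assumed) | Welch t, SDs 1.9 and 1.2 (assumed) |
|---|---|---|---|
| Normal | 4.8% | 5.3% | 4.9% |
| Clipped normal | 5.6% | 6.1% | 5.3% |
| Scaled beta | 6.1% | 14.8% | 4.8% |
| Gamma | 6.8% | 18.0% | 5.5% |

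Other runs, including some with identical distributions in both arms and some with other common means, gave two-stage type I error from 4.4% to 6.3% at the documented SDs. Across all runs at those SDs the tests disagreed in about 2% to 8% of trials.

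**The case against.** The rule is itself prespecified, and a normality check does not require sight of the group comparison. Section 2.5 keeps the analysts blind. The article condenses a fuller protocol, and a normality criterion or an endpoint-specific model may sit in an analysis plan that is not shown. With the documented SDs almost nothing changes numerically: under normal data the switch costs a fraction of a power point, and under skew the rule gains power because Mann-Whitney is then the stronger test.

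Most of this stands, and it limits how far the point goes. A reader might infer three stronger things that the protocol does not support:
- **That the test could be picked after seeing both results.** Nothing in the text says so, and the blinding in section 2.5 counts against it.
- **That the rank test is the likely branch.** The protocol gives means and SDs but no shape, and the switching rate runs from about 10% to 97% over plausible shapes.
- **That type I error is badly inflated.** The 15% to 18% figures need SDs of 1.9 and 1.2, which are assumed and more unequal than the pilot's 1.49 and 1.28, together with beta or gamma skew. With clipped normal data the same SDs give about 6%.

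The objection does not remove the central point. Section 2.9 states a rule, so this is more than a detail left to an analysis plan, and blinding does not settle which effect is being tested.

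**Conclusion.** The concern holds as a defect of definition. The primary hypothesis and effect measure depend on the observed distribution, through a criterion that is not given, while the sample size rests on a difference in means. It does not show a materially underpowered trial: t-test power is about 90% at 59 per group, and fixing Mann-Whitney outright would take 3 more evaluable participants per group under normality. It also does not show serious error inflation at the documented SDs, where two-stage type I error is about 4% to 6% and 6.8% at most.

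These sizes rest on assumed shapes and an assumed Shapiro-Wilk criterion. A different normality check would change the switching rates. It would not change the fact that the two tests target different quantities. The change is worth making because it is cheap and brings the analysis into line with section 2.3.

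**What to change.** In section 2.9, name one primary analysis for VAS that applies whatever the distribution: the difference between groups in mean post-treatment VAS, adjusted for baseline VAS, with a 95% confidence interval. Robust standard errors are optional. List Mann-Whitney as a named sensitivity analysis. With about 60 per group, comparing means does not need normally distributed scores: Welch's test stayed near 5% in the skewed simulations above.

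The cost is a sentence or two in section 2.9, and 59 evaluable and 66 enrolled per group need no change. The downside is some loss of power against the rank test if the data are strongly skewed: about 88% to 90% against 96% under the gamma shape, before any gain from baseline adjustment.

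### Baseline-adjusted analysis (ANCOVA) would sharpen the VAS comparison at almost no cost; the unadjusted t test in section 2.9 is valid but discards baseline information

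*Protocol article*

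**What the plan says.** Section 2.9 (Statistical Analysis) gives one rule for all measurement data: "independent sample t test is used for normal distribution", and the Mann-Whitney U test if the distribution is skewed. Both are two-group comparisons without covariates. The rule covers the primary outcome (VAS) and the two secondary scales (NDI and the Tanaka score). No baseline covariate is named anywhere in the article.

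Section 2.3 (Sample size) rests on a final value: "The calculation of sample size is based on the mean and standard deviation of the visual analogue scale", taken as the "score after treatment". The design inputs are "the experiment group is 2.41 ± 1.49, and the control group is 3.25 ± 1.28" and "Set α = 0.025, unilateral test, β = 0.10". The result is that "each group needs 59 participants, with an estimated withdrawal rate of 10%, and each group will include 66 participants".

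Section 2.7 (Evaluation criteria and efficacy judgment) says that the VAS "will be used to evaluate patients’ pain changes". It does not define a change-from-baseline variable.

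**The concern.** A patient's pain score after treatment usually depends partly on the score before treatment. An unadjusted test on the final score leaves that predictable variation in the error term. The trial then reports a wider interval than its own data would allow, and any chance imbalance in baseline pain passes into the estimate uncorrected.

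What is at stake is precision, not validity. The article has already committed to a specific test for these outcomes, so the question is whether a better one is available from the same patients and the same measurements. The wording in section 2.7 also leaves slightly loose whether the final score or the change is compared, and baseline adjustment would make that immaterial.

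**Working it through.** **Inputs from section 2.3.** Means 2.41 and 3.25; SDs 1.49 and 1.28; one-sided α = 0.025; power 0.90; 59 per group before withdrawals, 66 after.

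**Step 1: reproduce the stated sample size.**
- Difference: 3.25 − 2.41 = 0.84.
- Pooled SD: √[(1.49² + 1.28²)/2] = √[(2.2201 + 1.6384)/2] = 1.389.
- Standardised difference: 0.84/1.389 = 0.605.
- Standard error at 59 per group: 1.389 × √(2/59) = 0.2557; non-centrality 0.84/0.2557 = 3.28.
- Noncentral t power: 0.898 at 58 per group and 0.903 at 59, so 59 is the smallest number that reaches 90%.
- Withdrawals: 59/0.9 = 65.6, rounded up to 66.

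The stated 59 and 66 are therefore correct for an unadjusted t test on the post-treatment score. The matching 95% interval half-width is 1.98 × 0.2557 = 0.51, in the units of the section 2.3 figures.

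**Step 2: add baseline VAS as a covariate.** Neither the baseline-to-post correlation r nor the baseline SD is given. I assume a range for r and a common SD. The ANCOVA residual SD is then 1.389 × √(1 − r²), with 115 degrees of freedom at 59 per group. The interval shrinks by the factor √(1 − r²).

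| Assumed r | Residual SD | Power at 59 per group | Half-width | Narrower by |
|---|---|---|---|---|
| unadjusted t test | 1.389 | 90.3% | 0.51 | – |
| 0.2 | 1.361 | 91.4% | 0.50 | 2% |
| 0.3 | 1.325 | 92.7% | 0.48 | 5% |
| 0.5 | 1.203 | 96.4% | 0.44 | 13% |
| 0.7 | 0.992 | 99.5% | 0.36 | 29% |

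The percentages do not depend on the unit of the scale. The half-widths are in the section 2.3 units, whereas section 2.7 describes a 0 to 100 line.

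**Step 3: final score or change.** Write Y for the final score, X for baseline and T for treatment. If Y = a + τT + βX + error, then Y − X = a + τT + (β − 1)X + error. The treatment effect τ, its standard error and its P value are identical in both models. With baseline in the model, it no longer matters which quantity section 2.7 had in mind.

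**The case against.** The best reply is that nothing is broken. The test in section 2.9 and the quantity in section 2.3 agree, the sample size reproduces, and the test is unbiased under randomisation. A short article may also leave covariates to a fuller analysis plan. The first part stands, and it is why this is an improvement rather than a correction. The second only limits the point: the article does not leave the test open, since it names unadjusted ones.

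The gain can also be small. At r = 0.2 it is about one percentage point of power and a 2% narrower interval. That is fair, as r is unknown.

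A reader might infer something stronger: that the primary outcome is change from baseline, so the 90% power is in doubt. Under equal SDs, the SD of a change is 1.389 × √[2(1 − r)], and a t test on change at 59 per group would have 73% power at r = 0.2, 79% at 0.3, 90% at 0.5 and 99% at 0.7. The documents do not support that inference. It turns one loose phrase in section 2.7 into a defined endpoint, whereas the only place that ties VAS to a quantity for inference, section 2.3, uses the final score. The low figures need both that reading and a low assumed r.

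Nor does the unadjusted test produce a biased result. Chance baseline imbalance averages out over randomisations. Adjusting for it in the trial actually run is part of the same precision gain, not a further benefit.

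Finally, the visible text does not list a baseline VAS assessment. It is implied by evaluating pain changes, and the flow chart is not shown.

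**Conclusion.** This is a worthwhile improvement at almost no cost, not an error. The planned t test on the post-treatment VAS is valid and delivers its stated power, 90.3% at 59 per group. ANCOVA on the same patients would have between 91% (r = 0.2) and 99.5% (r = 0.7) power, with an interval 2% to 29% narrower. These figures rest on the section 2.3 means and SDs, an assumed r, equal baseline and final SDs, and a recorded baseline VAS. The direction of the gain holds at every r examined; its size cannot be fixed from the article.

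**What to change.** In section 2.9, replace the choice between t test and Mann-Whitney for the primary comparison with wording such as: the primary analysis is an ANCOVA of the VAS score at the end of the 4-week treatment, with treatment group as factor and baseline VAS as covariate; the adjusted mean difference is reported with its 95% confidence interval. Analyse NDI and the Tanaka score in the same way, each with its own baseline value.

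Keep 59 per group before withdrawals and 66 after, and note that the t-test calculation is conservative for ANCOVA. A repeated-measures mixed model is not needed for this purpose.

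The cost is one or two sentences. SPSS 18.0, already named in section 2.9, fits ANCOVA, and no extra patients are needed. The only thing to confirm is that the three scales are recorded before the first treatment session.
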